#### Data Management and Analysis

Quantitative data from the intervention study will be entered into Microsoft Excel and analyzed using SPSS for Macintosh, Version 25.0 (IBM Corp, Armonk, NY). ST on a weekday and weekend day will be calculated separately as per available literature [47]. So, the average ST (by viewing any type of media gadget) per day in a week will be calculated, and because there are 5 weekdays (Monday to Friday) and 2 weekend days (Saturday and Sunday) in a week, the weighted average ST per day in a week will be calculated as: Average ST per day (minutes) = [(Weekday ST in minutes x 5) + (Weekend ST in minutes x 2)]/7.

Continuous variables will be summarized as means with interquartile ranges and standard deviations. Correlations between a continuous variable and other variables will be estimated. Categorical variables will be summarized as proportions, and differences between groups will be tested using chi square tests. The data will be analyzed as per intention-to-treat analysis (for their initially assigned study arm) and per-protocol analysis. Relative risks and their effect sizes, together with the corresponding 95% CIs, will be estimated. The effectiveness of the intervention will be estimated by calculating the relative risk reduction (1-relative risk). A *P* value <.05 will be considered statistically significant for all analyses.

Information regarding PLUMS will be shared in the first communication and then reinforced every week for 8 weeks. So, participants who withdraw from the trial after the third week will be included in the analysis. Participants who withdraw any time before the third week will be excluded from the analysis.

Caregivers’ knowledge will be analyzed at the end of the intervention if no associations are observed. The proforma on behavior change will be completed at baseline (t_0_) and endline (t_1_) to determine the stage of change the families are at postintervention.

A feedback/compliance questionnaire (Supplementary Table 3 in Multimedia Appendix 5) will be given to the caregivers at each counseling session (weekly) to check their fidelity. The child's fidelity, including the level of engagement, will be checked with personalized journals comprising the activities they performed during the given intervention. The parents will be contacted via their preferred mode of communication weekly to keep them motivated and disseminate the next week's intervention module.

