## Abstract

**Background:**

Excessive digital screen exposure (≥1 hour per day) is associated with limited growth and development in children.

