## Introduction

### Background

The overall impact of sedentary behaviors on health across the lifespan has gathered widespread recognition, as it plays a significant role in most noncommunicable diseases (NCDs) [1]. The Sustainable Development Goals 2030 [2] envisions reducing premature mortality from NCDs by one-third via the prevention, treatment, and promotion of mental health and well-being. Around 34% to 94% of children aged 2 to 5 years remain sedentary during the day [3]. The prevalence of television (TV) viewing for more than 2 hours per day was reportedly 83% in the United States [4] and up to 82% in Canada [5] in children less than 5 years old and 78% in Australia [6] among children aged 3 to 5 years. A Thai study reported that children aged 1 year viewed TV for 1.23 (SD 1.42) hours per day, which increased to 1.69 (SD 1.56) hours per day when they turned 2 years old [7].

Early childhood is a crucial period that is marked by rapid growth and development [8]. Therefore, it is essential to correct an excessively sedentary lifestyle at an early age. These sedentary pursuits may have specific health consequences during this period and later in life [9]. The health effects of excessive screen time (ST) include behavioral problems; poor language, cognitive development, skills, memory, and executive function; lower social competence; sleep disturbances; depression; and low self-esteem [10-17]. In light of this, the present randomized controlled trial was planned with an assumption that ST might be causally associated with emotional behaviors, sleep behaviors, and children’s level of physical activity. ST of more than 1 hour per day among children aged 2-5 years is deemed excessive as per the American Academy of Pediatrics [18]. Similar guidelines are available in many developed countries (Australia [19], New Zealand [20], France [21], Italy [22], Canada [23], and World Health Organization [24]) for children aged 2-5 years.

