### Study Objectives

Given this background, the current study aims to develop a Program to Lower Unwanted Media Screens (PLUMS) to reduce ST among children aged 2-5 years and assess the effectiveness of PLUMS on reducing ST among children in Chandigarh, Union Territory, North India. Effectiveness of the intervention will be determined using the percentage risk reduction of mean ST in the intervention group compared to the control group. As excessive ST is a much less emphasized epidemic, this study's results might focus policy makers on this issue and help them formulate guidelines regarding ST use among young children in India and other low- and middle-income countries.

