#### Outcomes

The primary outcome (caregiver-reported) measure will be the mean change in ST (in minutes) per day separately for weekdays and weekends. The secondary outcomes (caregiver-reported) will be the mean change in the duration of physical activity (in minutes), proportion of children with emotional behavior problems, and sleep disturbances. For emotional behavior and sleep disturbances, the change in scores as per the tools will be noted, as mentioned earlier.

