## Discussion

### Principal Findings

Developing countries have seen a recent explosion in digital media, leading to increased ST and sedentary behavior in the younger generation [47]. However, the exact burden and impact of excessive ST exposure, especially among young children, are not well known. An Indian study concluded that 60% of the children (2-5 years) in North India used digital media gadgets for more than 1 hour per day. Bansal et al [48] from South India reported a 72% prevalence of ST for more than 1 hour per day (mobile usage only) among children younger than 15 years [48]. In addition, Indian children (3-11 years old) [49] and Korean children (2-5 years old) [47] experience ST of <1.4 hours per day and <1.21 hours per day, respectively. Since few local studies were available, the present study was planned to reduce the average mean duration of ST in children rather than the proportion.

Previous studies [38] have focused on the usage and impact of TV viewing in children; however, this study includes all digital media types being used by young children (3-5 years old). A systematic review suggested that the most effective interventions for ST reduction in children (0-5 years old) were ≥6 months in duration and conducted in a community setting [30]. Hence, in this study, a home-based intervention was developed to generate evidence on its effectiveness in reducing ST among young children from developing countries. This intervention includes providing feasible alternatives to ST and spending quality family time to strengthen parent-child bonding. Engaging children in goal setting [50] to decrease ST has been proven an effective measure. Also, the intervention plans to design workable measures to limit ST and improve the parent-child relationship in low- and middle-income countries. Further, involving children in alternative activities channels their energy, boosts their confidence, and decreases ST. Since there is evidence that there is a significantly higher risk of abnormal sleep with a TV in the bedroom [50], the interventions in this study include advising caregivers about changing the home media environment to decrease overall ST for children.

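### The protocol states effectiveness as a relative risk reduction, although the primary outcome and the sample size both concern a difference in mean screen time

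*Protocol article*

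**What the plan says.** Four sections of the protocol article concern means:

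- Outcomes: "The primary outcome (caregiver-reported) measure will be the mean change in ST (in minutes) per day separately for weekdays and weekends".
- Sample Size: a two-means formula, with an assumed difference in group means of 0.54 (no unit given), SDs of 2.09 (control) and 1.46 (intervention), two-sided 5% significance and 80% power. The result is 170 per arm, raised to 214 for attrition and nonresponse.
- Discussion, Principal Findings: "the present study was planned to reduce the average mean duration of ST in children rather than the proportion".
- Abstract, Methods: the primary outcome is again a mean change in ST duration.

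Two sections define effectiveness in terms of risk:

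- Study Objectives: "Effectiveness of the intervention will be determined using the percentage risk reduction of mean ST in the intervention group compared to the control group".
- Data Management and Analysis: "Relative risks and their effect sizes, together with the corresponding 95% CIs, will be estimated", followed by "The effectiveness of the intervention will be estimated by calculating the relative risk reduction (1-relative risk".

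The cut-off for excessive ST is worded in two ways. The Abstract has "Excessive digital screen exposure (≥1 hour per day", and the Introduction has "ST of more than 1 hour per day among children aged 2-5 years is deemed excessive".

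**The concern.** A relative risk compares the probabilities of an event. A mean number of minutes has no such probability, so one minus a relative risk cannot be computed for the primary outcome until ST is turned into a yes/no event. The analysis section names no such event. The Study Objectives phrase joins a risk to a mean and leaves the quantity undefined.

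What is at stake is how the main conclusion is reached. An analyst who follows the analysis section literally would have to choose an event, probably excessive ST, and base the effectiveness claim on it. That contrast is not the primary outcome and did not enter the sample size. Another analyst could reasonably report a ratio of means. If the text allows both, the choice can be made after the data are seen.

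**Working it through.** **1. What the sample size is built on.** Inputs from the Sample Size section: SDs 2.09 and 1.46, difference 0.54, two-sided 5%, 80% power.

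n = (2.09² + 1.46²)(1.960 + 0.842)² / 0.54² = 174.95, so 175 per arm.

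The stated 170 is 5 below this, or about 3%. The figure is therefore a two-means calculation, and no event rate or relative risk enters it. I keep 170 as the planned evaluable number.

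**2. Power for the difference in means.** The standard error at n per arm is √[(2.09² + 1.46²)/n].

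- n = 170: SE = √(6.4997/170) = 0.1955; 0.54/0.1955 − 1.96 = 0.80; power 78.9%.
- n = 214: SE = 0.1743; 0.54/0.1743 − 1.96 = 1.14; power 87.3%.

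**3. The same effect expressed as a relative risk (illustration).** Assumptions, none of them fixed by the protocol: 0.54 and the SDs are in hours per day; ST is normal; the common SD is √(6.4997/2) = 1.80; the whole distribution shifts by 0.54; the event is more than 1 hour per day. Control prevalence is taken from the Discussion: 60% (North India, ages 2-5) and 72% (South India, under 15 years, mobile use only).

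- Control mean = 1 + z(p) × 1.80. Intervention risk = Φ[(control mean − 0.54 − 1)/1.80].
- Power = Φ{[(p₁ − p₂) − 1.96 √(2p̄(1 − p̄)/n)] / √([p₁(1 − p₁) + p₂(1 − p₂)]/n)}, with p̄ the average of p₁ and p₂.

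| Control risk | Intervention risk | Relative risk reduction | Power at 170 per arm | n per arm for 80% |
|---|---|---|---|---|
| 60% | 48.2% | 19.7% | 59% | 277 |
| 72% | 61.2% | 15.1% | 56% | 296 |

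The Results section reports 440 enrolled. If split equally, that is 220 per arm before any attrition, which is still below 277 and 296. (The Abstract's 428 per arm is twice 214 and does not fit 440 enrolled. That is a separate discrepancy and is not used here.)

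**4. Sensitivity of the illustration.** A normal curve with these values puts Φ(−1.46/1.80) ≈ 21% of control children below zero ST at 60% prevalence, so real data must be skewed and the power figures are indicative only. Using the protocol's unequal SDs (2.09 in control, 1.46 in intervention) in place of 1.80, in the same formulas, gives intervention risks of 49.7% and 67.9%. Power at 170 per arm is then about 48% and 13%.

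**5. The ratio-of-means reading.** One minus the ratio of means equals 0.54 divided by the control mean. For assumed control means of 1.0, 2.0 and 3.0 hours this is 54%, 27% and 18%. The Sample Size section gives no control mean, so the design sets no percentage target either.

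**The case against.** The strongest reply is that the fault is one of vocabulary. Study Objectives speaks of a percentage reduction in mean ST, intervention against control. The natural reading is one minus the ratio of mean ST, which does address the primary outcome and can carry a confidence interval. The analysis section may simply repeat the misuse of the word risk. This stands as a possible reading of Study Objectives. It does not settle the matter, because the analysis section spells out one minus the relative risk and never says that a ratio of means is intended.

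A second reply is that relative risks have a proper place here. The Outcomes section lists the proportion of children with emotional-behavioral problems, and the Baseline Assessment section measures the prevalence of excessive ST. This is correct, and the fix keeps them for that use. Neither is the primary outcome, whereas the two effectiveness sentences are about the effectiveness of the intervention as such.

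A third reply is that an article may leave the test for a continuous outcome to the analysis plan. This also stands. A reader might infer from "Categorical variables will be summarized as proportions, and differences between groups will be tested using chi square tests" that the means will not be compared at all; the article does not support that inference, and the point does not depend on it. The objection is to a rule that is stated, not to one that is absent.

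The two wordings of the 1-hour cut-off are minor. They matter only if a relative risk for excessive ST is reported, and the article gives no ST distribution from which to count children at exactly 60 minutes.

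**Conclusion.** The inconsistency is in the current text. Outcome, sample size and stated rationale concern means, while the analysis section fixes a ratio of risks without defining an event. Under the assumptions shown, the literal rule would have about 56% to 59% power at 170 per arm, against about 79% for the difference in means. The size of that gap depends on normality, the unit, the common SD, the cut-off and the borrowed prevalences. The mismatch between outcome and effect measure does not.

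A reader might infer that the trial cannot answer its primary question, or that no power can be derived for a relative risk. Neither follows. The data and sample size suit a difference in means, Study Objectives admits a workable reading, and power for a relative risk can be derived once assumptions are added.

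**What to change.** In Study Objectives and in Data Management and Analysis, name the between-arm difference in mean change in ST (minutes per day), with its 95% CI, as the primary effect measure, preferably adjusted for baseline ST. The Results section says that ST will be measured again before delivery, so the text should say which measurement is the baseline.

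If a percentage is wanted, define it as one minus the ratio of mean ST (intervention over control), with a CI. Reserve relative risks and one minus the relative risk for binary secondary outcomes that are defined: emotional-behavioral problems, or excessive ST with a single cut-off used throughout. State the unit of the 0.54 and the SDs in the Sample Size section.

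Enrollment is complete and the intervention began in November 2020, so this needs a dated amendment with a short justification before the endline analysis. It needs no new data, no more participants and no new sample size, because the difference in means is the quantity that the calculation already uses.

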#### Blinding

Blinding will not be possible as the investigator will know the participants in the intervention group because he or she will motivate them to continue the intervention at each step. Also, the participants will know that they are being given an intervention to reduce the ST of their children. However, data entry will be performed by a data entry operator who will be blinded.

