#### Implementing the Intervention

In this stage, the PLUMS intervention will be delivered over an 8-week period at the household level in the intervention arm, as already described (Supplementary Table 2 in Multimedia Appendix 5). The objectives of the intervention are to reduce the ST of children [18], enable the caregivers with positive parenting skills and ST literacy, and propose unplugged family time in the home environment.

Participants in the intervention arm will also be classified into 5 behavior stages of change as per the transtheoretical model [45]. In the control arm, routine home-based and facility-based health services will be continued by the local auxiliary nurse midwife under the public health system. Compliance of the intervention will be checked via a proforma from parents (Supplementary Table 3 in Multimedia Appendix 5) and via a journal, videos, or pictures maintained by families.

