## Results

Enrollment of all participants (n=440) was completed during the baseline assessment. The intervention phase could not be started due to restrictions imposed under lockdown to contain the Covid-19 pandemic. Considering the Covid-19 pandemic and likely change in the ST and physical activity of the children, we will measure the ST and physical activity again before delivering the intervention. The intervention was started in November 2020. It will be implemented for 8 weeks. The endline assessment will be done immediately postintervention and after the 6 months of follow-up. The results will most likely be published by 2022.

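### Excluding everyone who withdraws before week 3 is incompatible with the stated intention-to-treat analysis and can bias the comparison; the rule belongs to the per-protocol set only

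*Protocol article*

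**What the plan says.** Three statements in Data Management and Analysis bear on who is analysed.

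- The analysis sets: "The data will be analyzed as per intention-to-treat analysis (for their initially assigned study arm) and per-protocol analysis".
- The reason for a cut-off: "Information regarding PLUMS will be shared in the first communication and then reinforced every week for 8 weeks". From this the article infers that "participants who withdraw from the trial after the third week will be included in the analysis".
- The exclusion: "Participants who withdraw any time before the third week will be excluded from the analysis".

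Neither the inclusion nor the exclusion sentence says which of the two analyses it governs.

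Implementing the Intervention shows who has a weekly programme: "the PLUMS intervention will be delivered over an 8-week period at the household level in the intervention arm". For the comparator: "In the control arm, routine home-based and facility-based health services will be continued". Under Blinding, "the participants will know that they are being given an intervention to reduce the ST of their children", and the investigator also knows the allocation. Under Postintervention Assessment, both arms are assessed immediately after the intervention (t1) and at 6 months (t2). Under Outcomes, the primary measure is the mean change in daily screen time.

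On timing, the Randomization section places data collection after allocation. Baseline Assessment dates the baseline data December 2019 to March 2020. The Results section then reports: "The intervention phase could not be started due to restrictions imposed under lockdown to contain the Covid-19 pandemic". Delivery began in November 2020.

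**The concern.** Intention-to-treat by assigned arm means that nothing happening after randomisation removes a family from the set. Withdrawal before week 3 is such an event. Both statements cannot govern the same analysis, and two analysts following this section could analyse different populations.

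The choice of cut-off makes this more than a labelling problem. Week 3 is a dose threshold: it marks how much programme content a family has received. Control families have no weekly module, so the third week has no programme meaning for them. Families also know which arm they are in, so leaving in the first two weeks may be a reaction to the programme. If those who leave would have shown a different change in screen time from those who stay, dropping them from one arm breaks the comparability that randomisation provided.

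**Working it through.** **Is the rule about exposure or about missing data?** The first outcome after the programme starts is collected at the end of the 8 weeks. A family that leaves the trial in week 2 and one that leaves in week 5 both lack a t1 outcome, yet only the first is excluded. The rule therefore sorts by exposure, which is a per-protocol criterion. Withdrawal during the third week itself is covered by neither sentence.

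**Whom does it reach?** Read literally, any time before the third week includes the gap between baseline (December 2019 to March 2020) and November 2020, about 8 to 11 months. On the article's own sequence these families were already allocated. Losses in that gap precede any PLUMS delivery and can fall in either arm.

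**How large could the effect be?** No stated figure depends on the rule. The planning values come from Sample Size: SDs 2.09 (control) and 1.46 (intervention), difference 0.54, two-sided Z = 1.96, 80% power. The formula there gives (2.09² + 1.46²)(1.96 + 0.84)²/0.54² = 174.8 per arm against 170 stated. That small gap has no bearing here.

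Assumptions:
- The unit of 0.54 and of the SDs is hours per day.
- The SDs apply to the analysed outcome.
- The 440 enrolled split equally (220 per arm), less the planned 10% loss to follow-up, giving n = 198 per arm.
- Exclusions occur in the intervention arm only, and there is no true effect.

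Let p be the share of the intervention arm excluded, and g the amount by which their mean change is worse than the full-arm mean. Then:

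- Spurious shift: b = p·g/(1 − p)
- SE = √(2.09²/n + 1.46²/(n(1 − p)))
- Two-sided type I error = Φ(b/SE − 1.96) + Φ(−b/SE − 1.96)

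Example with p = 10%, g = 0.9: b = 0.09/0.90 = 0.100 h. SE = √(4.3681/198 + 2.1316/178.2) = 0.1845. b/SE = 0.542, so the error is 8.4%.

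| p | g (h/day) | b (h/day) | b as % of 0.54 | SE | Type I error |
|---|---|---|---|---|---|
| any | 0 | 0 | 0% | – | 5.0% |
| 5% | 0.5 | 0.026 | 5% | 0.183 | 5.2% |
| 10% | 0.9 | 0.100 | 19% | 0.184 | 8.4% |
| 10% | 1.0 | 0.111 | 21% | 0.184 | 9.3% |
| 20% | 1.0 | 0.250 | 46% | 0.188 | 26.4% |

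With the planned 214 per arm instead of 198, the last four rows give 5.3%, 8.7%, 9.6% and 28.1%.

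**Can the sign reverse?** Yes. Suppose leavers start 0.9 h above the arm's baseline mean, the baseline-to-follow-up correlation is 0.5 with equal variances (both assumed), and there is no effect. Their expected change relative to the arm is (0.5 − 1) × 0.9 = −0.45 h, a larger fall than the rest. Dropping 10% of the arm then shifts the retained mean by 0.10 × 0.45/0.90 = 0.05 h against the intervention.

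**The case against.** The strongest reply is that the authors meant the rule to define the per-protocol set. It is the only text in the article that could do so, its reasoning is per-protocol reasoning, and the article is a condensed account. That intent is plausible, but the text does not say it, and the exclusion is stated rather than merely left to another document. The contradiction stands until one sentence removes it.

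Other objections succeed against stronger readings that a reader might draw:

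- *That the rule biases towards benefit.* It is tempting to argue that early leavers have the highest screen time, so removing them flatters the programme. But the primary outcome is change, and screen time is to be re-measured before delivery. A stable difference in level cancels, and regression to the mean can push the other way, as shown above. The documents give nothing on leavers' change.
- *That it acts only on the intervention arm.* The wording covers participants in both arms, and losses during the lockdown gap occurred before any programme contact. Only exclusions during the programme weeks have a reason to differ by arm.
- *That a type I error near 26% is to be expected.* The plan allows 10% loss for the whole study, so 20% in one arm before week 3 is an extreme case. The mild case is close to no inflation.
- *That deleting the rule cures the problem.* Families who truly leave the trial before week 3 have no t1 or t2 outcome to restore. Part of the calculated shift therefore reflects early dropout itself. How missing outcomes are handled may properly sit in an analysis plan that is not shown.

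**Conclusion.** The point holds as a conflict in the stated text: an exclusion based on a post-randomisation event, applied without restriction, is not compatible with analysing families in their initially assigned arm. Because the cut-off rests on exposure that only one arm has, in an unblinded trial, it can bias the comparison. The document does not establish that it will, or in which direction.

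The illustrated type I error of about 5% to about 26% is conditional on assumed values of p and g, one-arm exclusion, hours as the unit, and the planning SDs. It falls to the nominal 5% if exclusion is non-selective. The rule decides who enters the main comparison, so it should be corrected before the data are analysed.

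**What to change.** Reword the paragraph in Data Management and Analysis to state that:

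1. The intention-to-treat set contains every randomised family in its assigned arm, whatever the week of withdrawal, including withdrawals between allocation and the start of the intervention.
2. The week-3 threshold defines only the per-protocol (sensitivity) set, with withdrawal during week 3 assigned to one side.
3. The t1 and t2 questionnaires, already planned for both arms, are administered to all families who still consent to data collection, even if they have stopped the modules.

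The cost is a few sentences and some additional follow-up contacts. The estimate may be slightly less favourable. Families who withdraw consent entirely will still have missing outcomes, so the change reduces the problem without removing it.
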